## Abstract

**Introduction:**

Food-insecure households commonly rely on food pantries to supplement their nutritional needs, a challenge that was underscored during the COVID-19 pandemic. Food pantries, and the food banks that supply them, face common challenges in meeting variable client volume and dietary needs under normal and emergency (e.g., pandemic, natural disaster) conditions. A scalable digital strategy that has the capacity to streamline the emergency food distribution system, while promoting healthy food options, managing volunteer recruitment and training, and connecting to emergency management systems in times of need, is urgently required. To address this gap, we are developing a working mobile application (app) called the Support Application for Food PAntrieS (SAFPAS) and will evaluate its feasibility and impact on food pantry staff preparedness, stocking, and client uptake of healthful foods and beverages in two urban United States settings.

**Methods:**

This paper describes the protocol for a randomized controlled trial of the SAFPAS mobile application. We will conduct formative research in Baltimore, Maryland and Detroit, Michigan to develop and refine the SAFPAS app and increase scalability potential to other urban settings. Then we will test the app in 20 food pantries in Baltimore randomized to intervention or comparison. The impact of the app will be evaluated at several levels of the emergency food system, including food pantry clients (*n* = 360), food pantry staff and volunteers (*n* = 100), food pantry stock, and city agencies such as the local food bank and Office of Emergency Management. The primary outcome of the SAFPAS trial is to improve the healthfulness of the foods received by food pantry clients, measured using the Food Assessment Scoring Tool (FAST). Post-trial, we will conduct additional formative research in Detroit to prepare the app for scale-up.

**Discussion:**

We anticipate that SAFPAS will improve alignment in the supply and demand for healthy foods among food pantry clients, food pantries, and city agencies which supply food in Baltimore. Real-time, bidirectional communication between entities across the system allows for increased situational awareness at all levels during normal and emergency operations. By conducting formative research in Detroit, we hope to increase the scalability of the SAFPAS app to additional settings nationwide.

**Clinical trial registration:**

NCT87654321. https://classic.clinicaltrials.gov/ct2/show/NCT05880004.

## Introduction

1

In 2021, about 13.5 million households (10.2%) in the United States (US) reported experiencing food insecurity at some point during the year (1). Food-insecure households may rely on food pantries to supplement their nutritional needs. While US food insecurity prevalence remained stable during the pandemic, use of food pantries increased from 4.4% in 2019 to 6.7% in 2020 (2, 3). Among food-insecure households, 36.5% reported using a food pantry, and among households with a very low food security, 45.5% reported using a food pantry in 2020 (3). An increased need during the pandemic underscored the challenges commonly faced by food pantries, and the food banks that supply them, in meeting variable client volume and dietary need (4). For example, food pantries tend to have limited staff capacity and resources to provide a safe forum for client choice and to assist with making healthy selections (5, 6). Additionally, food pantries are largely limited in what they can offer by what they receive from the central food banks, and thus tend to stock fewer healthy options despite their desire to emphasize healthy foods (7). As a result, previous studies have indicated that food pantry clients have lower diet quality (8).

To this end, capacity building and communication are necessary at multiple levels of the emergency food system to better align the supply and demand for healthier food options at food pantries. There is currently no system in place to support bidirectional information flow from clients up through city-level agencies. Thus, it is difficult to communicate client preferences and food pantry needs to food banks and city agencies who can help direct resources to food pantries.

This critical need during normal operations becomes even more pronounced during emergency situations (e.g., pandemic, natural disaster) to ensure access to consistent, nutritionally adequate food for pantry clients, and to provide real-time, data-driven situational awareness (5) of population health vulnerabilities. For example, personal communications between the research team and Baltimore City food pantries and city agencies revealed that city agencies and clients had no way of knowing which food pantries were open during the pandemic, needed supplies like PPE, or could accept new clients.

Digital strategies offer a promising solution given the ubiquity of smart phone use and evidence from multiple fields of research that digitizing can streamline operations and communications (9–12). The emergency food system has already started to move in this direction: food banks often have online reporting portals for food pantries, and other apps exist to address client tracking and inventory management (12, 13). However, many food pantry operations (e.g., volunteer management, training, and communication, client choice, and communications with city agencies) are outside the scope and capabilities of existing applications, and there is no “one-stop-shop” that houses all necessary functions (12). Importantly, there is interest among food pantry directors nationwide for a digital solution to enhance pantry management and operations (14).

Thus, a scalable digital strategy that promotes healthy foods at multiple levels of the emergency food system, streamlines food distribution efforts at each level, provides a mechanism for volunteer recruitment and training, enhances access to healthy foods, and connects with emergency management systems in times of need, is urgently required. The timeliness of such a digital strategy is further underscored by the lessons learned from COVID-19 and the looming expectancy of future disasters and emergencies. To fill this gap, we are developing a Support Application for Food PAntrieS (SAFPAS or “safepass”) working mobile application (app), and evaluating its feasibility and impact on food pantry staff preparedness, stocking, and client uptake of healthful foods and beverages. In this paper, we describe the protocol for this randomized controlled trial of the SAFPAS mobile application. The aims of the SAFPAS trial are to:

Develop a technically functional digital tool to improve food pantry services in low-income food settings;Implement a randomized controlled trial of the SAFPAS app in Baltimore, Maryland and assess its feasibility;Evaluate the impact of the SAFPAS app on the healthiness of foods received, food security, and food-related psychosocial factors by food pantry clients in a sample population of low-income urban clients in Baltimore, Maryland; andEvaluate the impact of SAFPAS on food pantry stocking, staff capacity, and emergency preparedness and response in Baltimore, Maryland.

Formative research will be conducted in Detroit, Michigan pre- and post-trial to refine the app and increase the potential scalability to other urban settings outside of Baltimore, Maryland in a future, NIH R01 trial. Detroit was selected given existing partnerships with researchers, food banks, and food pantries in that area, and the sociodemographic similarities with Baltimore, and will be included in a future trial. Funding limitations did not allow piloting of the app in multiple localities.

## Methods

2

### Overview

2.1

There are four main phases of data collection in the SAFPAS trial. First, we will conduct formative research in Baltimore, Maryland and Detroit, Michigan to refine the app prototype images and inform the development of the working app. Second, we will develop a stable working version of the app, and conduct functionality, stability, and usability testing (in Baltimore only). Third, we will employ a randomized controlled trial design (in Baltimore only) over a 12-month period to test the app and assess preliminary feasibility and impact at the food pantry and food pantry client levels. Finally, after the trial, we will conduct additional formative research in Baltimore and Detroit using the improved version of the app to prepare for scaling for use in different settings. The conceptual framework for the study is presented in Figure 1.

**Figure 1 fig1:**
[figure not shown]
Conceptual framework guiding the SAFPAS trial. The green shaded boxes indicate SAFPAS app features. The intervention points are labeled with orange stars, and the evaluation measures (pre- and post-trial) are indicated with blue circles. HEI, healthy eating index; BMI, body mass index; FAST, food assessment scoring tool scores.

Evidence supporting the use of mobile apps to improve general health outcomes and disease management has been mixed; few studies have examined its utility among food insecure populations, and those which have are limited (15–17). However, authors note a lack of critical details about the development and user-centered design methods utilized to develop, and insufficient detail about testing the app in terms of usability, user-friendliness, and implementation (15, 16, 18). This study contributes to this growing area of the literature by providing app development and testing details, as well as by using a randomized-controlled trial to assess initial impact in a population experiencing food insecurity. Several other studies have employed a randomized-controlled trial to evaluate mobile apps (15, 16, 18–22).

### Setting

2.2

Baltimore is the largest city in Maryland and is estimated to have nearly 570,000 residents, of which 61.6% are Black (23). Prior to the COVID-19 pandemic, 18% of residents experienced food insecurity, increasing to 21.7% following the COVID-19 pandemic (24). The Maryland Food Bank (MFB), founded in 1979 as the first food bank on the US east coast, is headquartered in Baltimore County, Maryland and supplies more than 300 food pantries, serves over 1,220 partners (soup kitchens, food pantries, shelters, etc.) across the state, and distributes more than 102,000 meals daily.

Detroit is the largest city in Michigan and has a population of 620,000 residents, of which 78% are Black (25). Estimates of food insecurity in Detroit vary, ranging from 30–70% of households (26, 27). Two food banks serve the Detroit area: Gleaners Community Food Bank and Forgotten Harvest (28). Gleaners works with more than 400 partner agencies and distributes over 47 million pounds of food annually (29). Forgotten Harvest has over 200 partner agencies and distributes 42 million pounds of food annually (30).

In order to optimize the app for use in low-resource contexts, we focused on both front-end and back-end improvements (31–37). For the front-end, we prioritized a lightweight, responsive design using React Native, HTML, and CSS, ensuring compatibility with older mobile devices and reducing resource consumption. On the back-end, we employed techniques such as API tuning, compression, caching, and server-side rendering to enhance performance and minimize data transfer. Cloud infrastructure from providers like AWS or GCP further supports scalability and availability. To address intermittent internet access, we implemented offline capabilities using PouchDB and CouchDB, enabling data storage and synchronization when connectivity is available. These efforts aim to overcome technology limitations and improve user experience (31–37), with findings informing future initiatives in similar environments.

### Formative research

2.3

#### Formative research prior to funding

2.3.1

This study builds upon extensive prior formative research, including sharing a series of low- and high-fidelity wireframe mockup images designed collectively by the research team with food pantry directors, previous intervention work in Baltimore food pantries (7, 38), two scoping reviews of the literature (12, 13), and a national survey of food pantry directors (14). Across this work, we found that food pantries in Baltimore experienced challenges related to finding a sufficient number of staff/volunteers, provide client choice and support clients in making healthy choices, and lacked emergency preparedness and response training. Among our food pantry partners and study participants, we found widespread support for a multi-featured app that would permit food pantry leaders to track pantry statistics, enhance all aspects of managing staff/volunteers and clients (called ‘neighbors’ in Maryland, and are referred to as such in the app) under both normal and emergency situations, and provide a remote and therefore safer version of client choice.

#### Additional formative research

2.3.2

The first phase of this trial is additional formative research in Baltimore and Detroit to aid the design of the app. This includes interviewing food pantry staff and volunteers, and clients in both locations, and interviewing key staff from city agencies in Baltimore. We will purposively recruit food pantry directors, volunteers and staff from Baltimore (*n* = 12) and Detroit (*n* = 8); regular food pantry clients from Baltimore (*n* = 20) and Detroit (*n* = 15); and food bank personnel from the MFB (*n* = 6) and Gleaners Community Food Bank in Detroit (*n* = 4). In Baltimore we will also recruit key staff from city agencies such as the Health Department, Department of Planning, and Office of Emergency Management (*n* = 6). The sample size goals were generated based upon expected point of saturation given the specificity of the topic (39) as well as pragmatic considerations (e.g., budget and timeline constraints).

To be eligible, all interviewees must be at least 18 years old. Food pantry volunteers and staff must have worked with the food pantry for at least one year, plan to work at least one more year at the same food pantry, and have access to a smartphone or other device to access the web so they can use the app. Food pantry clients must be existing regular users of the food pantry as identified by the food pantry, must not anticipate moving out of Baltimore or Detroit for one year, have access to a smartphone, and be willing and able to use a web app through the smartphone to order food from food pantries. City agency staff must work for one of the relevant city agencies or food banks mentioned above. Interested and eligible interviewees will be invited to participate in a 45–60 min interview either via Zoom or in-person depending upon their preference. All interviewees will receive a $20 Visa Vanilla gift card for participating.

During the interviews, we will present high-fidelity wireframe mockup images of the different proposed features of the app, which provide snapshots of each app screen, to stimulate discussion around the look and design of the app, functionality, and what could be improved/changed about the app to better align with users’ needs. We will update the wireframe images iteratively based on these discussions. At multiple points throughout the formative phase, data collectors will present the feedback received from interviewees to the study team during weekly meetings. The research team will discuss each suggestion and decide whether to make the change/addition to the app based on data saturation and feasibility within the budget and timeline constraints of the study. If the team agrees the change applies to a wide range of pantries and is feasible, the wireframe images will be updated accordingly. The newly updated wireframes will then be used for subsequent interviews, and the process will begin again.

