### Randomized controlled trial

2.4

For the trial, which will only take place in Baltimore, we will recruit at the food pantry level. We will recruit 10 intervention and 10 control food pantries from a list of member food pantries provided by the Maryland Food Bank, foodpantries.org, listings maintained by colleagues who do work with food pantries, and The Maryland Food System Map list. Only medium and large food pantries will be recruited (>10,000 pounds of food distributed per year) given that small pantries may few staff, volunteers, and clients, and may be open infrequently. Food pantries that have participated in our trials previously will be excluded from participation, as will school- and health-center- based pantries given their potential different distribution systems compared to traditional food pantries. Once a pantry is recruited, we will recruit staff and volunteers (*n* = 100, 5 per pantry), and clients (*n* = 360, 18 per pantry) to be part of the trial using the same inclusion criteria described for formative research. These recruitment numbers are the goal reflect the results of a power and sample size calculation based on showing change in FAST scores.

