### Intervention trial description

2.8

The trial will be conducted in 3 stages (4 months each), differentiated by the types of SAFPAS features activated (Table 1). During the first weeks of each stage, formal training of participating food pantry directors/staff and MFB staff will take place – focusing on the use of any new features. Initial training will be followed up by proficiency testing in which pantry staff will be requested to complete certain functions (e.g., register a new client, locate an order, send a message). With each subsequent stage, additional app features will be made available to users to test. We will take this phased approach to introducing app features to allow time for training users on each feature; and by introducing a few features of the app at a time, we will have the opportunity to receive feedback and update the app as needed (see Table 1).

**Table 1 tab1:** SAFPAS app feature implementation phases by user type.

SAFPAS user	Phase 1	Phase 2	Phase 3
	Features introduced		
Client	Volunteer application, Pantry locator, Nutrition education messaging, Communications center	eChoice	Receive emergency information
Pantry staff and volunteers	Staff and volunteer management, Staff and volunteer training, Communications center, Information dashboard	eChoice	Bi-directional emergency information
Maryland food bank/City agency staff	View/access training materials, Communications center, Information dashboard	eChoice	Bi-directional emergency information

The SAFPAS app will have three main modules based on the three different intended user types: clients, food pantry staff and volunteers, and the Maryland Food Bank/city agencies.

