### Comparison group

2.9

The 10 food pantries in the comparison group will be introduced to the SAFPAS app after the intervention, including post-intervention data collection, is complete.

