#### Food pantry staff and volunteer-level instruments

2.10.2

A Food Pantry Staff/Volunteer Impact Questionnaire will be developed to assess food pantry staff/volunteer knowledge and behaviors related to nutrition, food hygiene, and emergency management in about 100 participants (approximately 5 per pantry). Pantry managers/staff will be selected on the basis of seniority, with preference given to more senior staff, and those who intend to continue working in the pantry for at least one year. Questions will correspond to the information presented in the SAFPAS training modules and will be measured at baseline and post-intervention.

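### The one-year stay criterion used for trial clients and staff ends before the post-intervention measurement is due, so a few people who already expect to leave before it can still be enrolled

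*Protocol article*

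**What the plan says.** The stay criteria are set in section 2.3.2 for the formative interviews. Clients "must not anticipate moving out of Baltimore or Detroit for one year", and staff and volunteers must "plan to work at least one more year at the same food pantry". Section 2.4 carries both into the trial by cross-reference: staff, volunteers and clients are recruited "to be part of the trial using the same inclusion criteria described for formative research". Section 2.10.2 repeats the horizon for the staff questionnaire, as a preference in selection for "those who intend to continue working in the pantry for at least one year".

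On timing, section 2.1 describes a randomised trial "over a 12-month period to test the app and assess preliminary feasibility and impact". Section 2.8 fills that period with intervention: "The trial will be conducted in 3 stages (4 months each"). Section 2.10 places evaluation at baseline and after the intervention, and section 2.10.1 measures the same clients both times. Section 2.9 gives comparison pantries the app only "after the intervention, including post-intervention data collection, is complete", which makes the post-intervention fieldwork a further step. Under section 2.11 the primary outcome is each client's post-intervention FAST score minus the pre-intervention score.

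**The concern.** A stay criterion in a cohort measured twice is there to screen out people who already know they will be gone at the second measurement. To do that, its horizon must reach the second measurement. Here the horizon equals the length of the intervention alone and leaves no room for fieldwork at either end.

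What is at stake is completeness of the primary outcome. A client with a baseline bag and no post-intervention bag has no change score. Some of that loss could be foreseen at screening and so avoided, and it would draw on an allowance meant for loss that cannot be foreseen. The same applies to the staff questionnaire, although its results are secondary.

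**Working it through.** **1. The plan's own figure.** 3 stages × 4 months = 12 months. This reproduces the 12-month period in section 2.1 and equals the whole of the one-year criterion.

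**2. Does baseline come before stage 1?** Yes, by inference. Section 2.8.1 says that clients' baseline questionnaire responses help shape the nutrition education messages, and Table 1 lists that messaging as a Phase 1 feature. Baseline data must therefore exist before, or at the latest when, stage 1 opens.

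**3. Does the post-intervention measurement come after stage 3?** Section 2.10 calls it post-intervention, and section 2.9 treats its completion as a step of its own.

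**4. Interval to be covered.**

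Interval = lead (baseline to start of stage 1) + 12 + lag (end of stage 3 to post-intervention measurement)

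Uncovered time = interval − 12 = lead + lag

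The article gives neither lead nor lag, and it does not say when the one-year clock starts. Taking the clock from the baseline visit, with assumed values:

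| Assumed lead (months) | Assumed lag (months) | Interval (months) | Uncovered (months) |
|---|---|---|---|
| 0 | 0 | 12 | 0 |
| 0.5 | 0 | 12.5 | 0.5 |
| 1 | 1 | 14 | 2 |
| 3 | 3 | 18 | 6 |

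The first row requires baseline on the day stage 1 opens and the post-intervention measurement on the day stage 3 closes. That is unrealistic for all 360 clients at 20 pantries, given bag weighing, a questionnaire, a food frequency questionnaire and anthropometry. If the clock ran from the start of stage 1 instead, the uncovered time would be the lag alone.

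**5. Dropout allowance.** Section 2.11 adds 3 clients per pantry to reach 18: 3/18 = 16.7%. One foreseeable leaver uses 1 of those 3.

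**6. Cost in power.** Inputs from section 2.11: difference 12 points, effect size d = 0.8 (implied SD 12/0.8 = 15, read as the SD of individual changes), intraclass correlation 0.2, two-sided 5%. For a cluster-level t-test with k pantries per arm and m clients per pantry:

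noncentrality = d / √(2 × [1 + (m − 1) × 0.2] / (k × m)), df = 2k − 2

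Before the allowances (k = 9, m = 15), power is 88.6%. The planned 80% is not reproduced exactly, but on this reading the plan errs on the safe side: at m = 15, 8 pantries per arm give 84.0% and 7 give 77.9%. With k = 10:

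| Clients measured per pantry | Noncentrality | Power |
|---|---|---|
| 18 | 0.8/√(2 × 4.4/180) = 3.62 | 92.8% |
| 15 | 0.8/√(2 × 3.8/150) = 3.55 | 91.9% |
| 12 | 0.8/√(2 × 3.2/120) = 3.46 | 90.6% |
| 10 | 0.8/√(2 × 2.8/100) = 3.38 | 89.2% |

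Power depends mainly on the number of pantries, so losing some clients within each pantry changes it little.

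**The case against.** The strongest reply is that this is a rounding matter. A one-year stay, a smartphone and willingness to order food through an app make little sense for a single interview. They suggest a criterion written with a nominal 12-month trial in mind, so the wording need not be a careless import. The people it lets through are only those who, at screening, expect to leave after month 12 but before their own post-intervention visit. No document suggests how many such people there are. The plan already allows for attrition, with 3 extra clients per pantry and one extra pantry per arm, and on its own inputs it keeps power near 89% even if 8 of 18 clients are lost everywhere. The staff wording is a minimum, and in section 2.10.2 it sits within a selection preference.

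Most of this stands, and it limits the point to a minor one. It does not remove the mismatch: whatever the criterion's origin, its horizon ends where the intervention ends, and the outcome is measured after that. A minimum of one year still admits someone who plans to leave at one year.

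A reader might also infer that a client who plans to move in month 13 is certain to be lost. The documents do not support that. If the interval is 12.5 months, someone leaving late in month 13 has already been measured. Section 2.10.1 ties measurement to the school or the pantry rather than to residence, so moving away makes loss likelier without proving it.

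**Conclusion.** The point holds as a minor defect in a stated eligibility rule. The one-year horizon covers the intervention but neither fieldwork window, so some foreseeable missing change scores are allowed in that a change of wording would keep out. The direction follows from the article's own schedule. The size of the gap does not: weeks to a few months is an assumption, and an interval of 14 to 18 months should not be read as a figure from the plan. The number of people affected is unknown and probably small, because the window is narrow.

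Two stronger readings should be set aside. The first is that the trial's power is threatened: with the effect size read on the individual scale, going from 18 to 15 clients per pantry costs 92.8 − 91.9 = 0.9 percentage points. The second is that staff loss uses up an allowance of 5 per pantry: 5 is the staff sample itself, no staff dropout allowance is stated, and section 2.11 says the study is not powered for secondary outcomes.

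**What to change.** In section 2.4, stop importing the one-year horizon for trial participants and state a trial-specific one. For clients: *does not expect to move away from Baltimore before the post-intervention measurements have been completed*. For staff and volunteers, in sections 2.4 and 2.10.2: *does not expect to leave the pantry before the post-intervention measurements have been completed*. Leave the criterion in section 2.3.2 as it is for the formative interviews.

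The timeline argument does not support a further exclusion for clients who expect to stop using their home pantry. That would be a separate decision.

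The cost is a change of eligibility wording, a matching change to the screening question and a slightly smaller eligible pool. Design, sample size and analysis are unaffected. The change helps only participants screened after it is made, so it belongs before enrolment.
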